**Methods:**

We plan to monitor a cohort of patients with high-lethality cancers treated in the public health system of Catalonia between 2006 and 2012, retrospectively, for survival for 5 years after diagnosis or until death. A control cohort, comprising people without cancer, will also be retrospectively monitored for 5 years. The following study variables will be extracted from different population databases: type of cancer (patients with cancer cohort), date and cause of death, pharmacological treatment, sex, age, and place of residence. During the first stage of statistical analysis of the patients with cancer cohort, the drugs consumed by the long-term survivors (alive at 5 years) will be compared with those consumed by nonsurvivors. In the second stage, the survival associated with the consumption of each relevant drug will be analyzed. For the analyses, groups will be matched for potentially confounding variables, and multivariate analyses will be performed to adjust for residual confounding variables if necessary. The control cohort will be used to verify whether the associations found are exclusive to patients with cancer or whether they also occur in patients without cancer.

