### Statistical Analysis

To achieve the primary objective, several exploratory analyses will be performed. These will look for an association between the use of the different drugs available in the database (the exposure variable) and patient survival (the outcome variable). The exposure variable will be treated both dichotomously (exposed or not exposed) and quantitatively. The time exposed to the drug, the average monthly dose, the maximum dose, or the cumulative dose per unit of time will be considered. Specific analyses will be carried out on the effect of 2 or more drugs that have been shown to influence survival when they have been consumed, either simultaneously or sequentially, within the time unit being analyzed. The outcome variable is survival during the observation period. Patients who are censored, for whom no death is recorded during the follow-up time, are considered alive at the end of the period.

In addition to the machine-learning techniques described above, the association between exposure and outcome will be investigated using 2 different approaches. The exposure odds for each drug will be calculated, and this exposure will be compared between patients considered alive at 5 years and those who have died using odds ratios (exposure odds ratio). The group of nonsurvivors will be selected with different time criteria in a sensitivity analysis: deceased in the 1st, 2nd, or 3rd year after diagnosis. Second, the survival time of participants exposed and unexposed to each drug available in the database (individual agents, ATC5 codes) or to each family of agents (ATC4 codes) will be compared.

To avoid bias due to a lack of randomization, in both approaches, matching will be carried out between the groups with respect to confounding variables. In addition, if residual confounding is suspected or an imbalance between groups remains after matching, adjustments for age, sex, and diagnostic groups will be performed. A Cox regression model will be constructed to estimate the effect of the evaluated drug. The hazard ratio (HR) and its 95% CI will be reported. Hazard proportionality will be assessed graphically by Schoenfeld residuals.

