
### Sample Size Considerations

Based on a maximum 5-year survival probability of 20% (P=.2, *Q*=.8) and with a significance level of 5% (95% CI) and a power of 80%, it will be possible to detect a difference of 10% between 2 groups with 294 individuals per group. Table 2 shows an initial estimate of the number of survivors at 5 years available during the study period. According to preliminary data not shown, the database available for the study includes a total of 102,860 patients diagnosed with the cancers under study.

**Table 2 table2:** Incidence and estimated survival for the main pathologies under study.

Cancer	New cases each year, n	Estimated 5-year survival, n (%)	Cumulative survivors throughout the study, n
Lung	4079	738 (18.1)	3691
Metastatic colon	6128	852 (13.9)	4259
Metastatic bladder	2444	122 (5)	611
Metastatic kidney	1094	131 (12)	656
Metastatic melanoma	860	171 (19.9)	856
Pancreas	1168	96 (8.2)	479
Esophagus	616	116 (18.8)	579
Metastatic stomach	1089	57 (5.2)	283
Liver	670	118 (17.6)	590

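### The odds-ratio screen matches survivors to non-survivors but ties adjustment to leftover imbalance, so an odds ratio left unadjusted because the groups balance is biased toward 1 when matching factors predict drug use

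*Protocol article*

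**What the plan says.** The Statistical Analysis section of the Protocol article describes two approaches besides the machine learning. The first groups patients by outcome and compares their drug exposure: "this exposure will be compared between patients considered alive at 5 years and those who have died using odds ratios (exposure odds ratio"). The second groups patients by exposure and compares "the survival time of participants exposed and unexposed to each drug available in the database".

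Matching applies to each: "in both approaches, matching will be carried out between the groups with respect to confounding variables". The matching variables, the ratio, and whether matching is individual or by frequency are not given.

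The section then fixes when adjustment is made: "if residual confounding is suspected or an imbalance between groups remains after matching, adjustments for age, sex, and diagnostic groups will be performed". The Methods paragraph of the Abstract has the same conditional rule: "groups will be matched for potentially confounding variables, and multivariate analyses will be performed to adjust for residual confounding variables if necessary".

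The section also plans a Cox model. It does not say whether the odds ratio is conditional or unconditional.

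**The concern.** One adjustment rule is written for two designs that behave differently. When exposed patients are matched to unexposed patients, balance on a factor means that this factor no longer confounds the comparison. When survivors are matched to non-survivors, balance on a factor only shows that the matching worked. Matching on outcome makes the exposure distributions of the two groups more alike to the extent that the factor predicts drug use, and only an analysis that conditions on the factor undoes this. In the outcome-matched approach the imbalance part of the rule therefore takes good balance as the reason to leave out factors that have to stay in.

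Three things are at stake.

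- The study is a screen, and the attenuation depends on how strongly each drug's use follows a matching factor. It differs between drugs and can distort their ranking.
- Findings that recur in the control cohort are discarded. If the odds ratio is attenuated there too, a general effect on survival may fail to recur and be kept as if it were specific to cancer.
- The Discussion accepts one bias toward the null, from late registration. This would be a second, unacknowledged and avoidable.

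**Working it through.** **The plan's own figure.** Sample Size Considerations says "it will be possible to detect a difference of 10% between 2 groups with 294 individuals per group". With 20% vs 30%, two-sided 5% and 80% power:

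n = [1.96·√(2·0.25·0.75) + 0.842·√(0.2·0.8 + 0.3·0.7)]² / 0.10² = 293.2, so 294 per group.

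This reproduces the figure. It is a formula for unmatched groups, and the point below does not change it.

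**Unconditional vs matched odds ratio.** Let stratum s of the matching factors hold a share w of the pairs. Let p0 be the exposure probability of the non-survivor, and let the survivor have odds(p1) = 2·odds(p0), a true within-stratum odds ratio of 2.

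- Unconditional: P1 = Σw·p1, P0 = Σw·p0, OR = [P1/(1−P1)] / [P0/(1−P0)].
- Matched (1:1): OR = Σw·p1(1−p0) / Σw·p0(1−p1). This equals 2 in every case below.

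The exposure patterns are assumptions, since the document gives none.

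1. Five equal strata, p0 = 5, 15, 25, 35, 45%. P0 = 0.250, P1 = 0.379. OR = 0.6105/0.3333 = **1.83**.
2. A matched disease in 20% of pairs, drug use 40% with it and 5% without. P0 = 0.2·0.40 + 0.8·0.05 = 0.120; P1 = 0.2·0.5714 + 0.8·0.0952 = 0.1905. OR = 0.2353/0.1364 = **1.73**.
3. The same, with use 60% and 1%. P0 = 0.128; P1 = 0.2·0.75 + 0.8·0.0198 = 0.1658. OR = 0.1988/0.1468 = **1.35**. It is 1.35 to 1.43 if the disease is present in 10% to 50% of pairs.
4. A matching factor unrelated to use (p0 = 20% throughout). OR = **2.00**, no bias.

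**The test under no effect.** The odds ratio is then 1 either way, but a test that ignores the pairing is conservative. The within-pair correlation of exposure is φ = Var(p0)/[P0(1−P0)], and the true two-sided error is 2Φ(−1.96/√(1−φ)).

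| Pattern | φ | Error of nominal 5% test |
|---|---|---|
| 1 | 0.02/0.1875 = 0.11 | 3.8% |
| 2 | 0.0196/0.1056 = 0.19 | 3.0% |
| 3 | 0.0557/0.1116 = 0.50 | 0.6% |

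**Power and interval coverage (normal approximation, true odds ratio 2).** At 294 pairs, power ignoring the pairs vs conditional is 93% vs 94%, 67% vs 73%, and 16% vs 47% for patterns 1 to 3. With 3,691 pairs (the cumulative lung survivors in Table 2), power is near 100% either way. The unadjusted 95% interval then covers the true value about 60%, 37% and 0% of the time. A large database restores power but not validity.

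**A second model.** Take a true odds ratio of 1.71, which is (0.3/0.7)/(0.2/0.8), the odds ratio of the plan's 30% vs 20%. Use 294 pairs, with an assumed exposure prevalence of 20% and an assumed normally distributed matching score.

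| Odds ratio of exposure per SD of score | OR, pairs ignored | OR, conditional | Power, ignored vs conditional |
|---|---|---|---|
| 1 | 1.71 | 1.71 | 80% vs 80% |
| 2 | 1.64 | 1.71 | 74% vs 76% |
| 5 | 1.47 | 1.71 | 51% vs 64% |
| 10 | 1.38 | 1.71 | 33% vs 55% |

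With prevalence 5%, 20% or 50% and a binary or normal factor, the unadjusted value lies between about 1.35 and 1.71, and the power loss between 0 and about 25 points.

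**The Cox approach, for contrast.** Simulation of 294 exposure-matched pairs, true conditional hazard ratio 0.75, matching-factor hazard ratio per SD of 1, 1.5 and 2.5 (assumed):

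- Hazard ratio ignoring the matching: 0.75, 0.77, 0.81. This is the marginal hazard ratio, which differs from the conditional one by non-collapsibility. It is not bias from matching.
- Power ignoring the matching: 87%, 82%, 60%.
- Power with covariate adjustment: 87%, 87%, 85%.
- Power with stratification by pair: 67%, 66%, 62%.

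**The case against.** The strongest reply is that the article never prescribes a crude odds ratio. An exposure odds ratio is an effect measure, and conditional logistic regression also yields one. The Introduction calls this a general protocol and leaves methodological detail to the papers on each substudy, so the estimator may be fixed in a document not shown. This stands as far as the estimator is concerned. It does not reach the adjustment rule, which the article states twice and which points the wrong way for outcome-matched groups.

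Second, the rule has two triggers. Adjustment also follows if residual confounding is suspected, and the Discussion concedes unmeasured confounders, so adjustment could be made even in balanced groups. A reader might infer that the trigger is always off after good matching; the text does not support that. But an analyst who sees balance and suspects nothing further is told not to adjust. The fallback covariates (age, sex, diagnostic groups) also need not cover every matching variable.

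Third, the sizes rest on assumed patterns. No passage says that survivors are matched on a drug's indication, which is the kind of factor behind the largest figure. This stands.

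Fourth, the analyses are exploratory, a true null stays at 1, and the same drugs are also screened by survival time and by rule mining. This limits the consequence. It is no reason to keep an avoidable bias in one of the two main statistical approaches.

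**Conclusion.** The point holds for the outcome-matched odds ratio. Where the matched survivors and non-survivors are balanced and adjustment is omitted for that reason, the odds ratio is biased toward 1 and its test is conservative whenever the matching factors are related to drug use. With a true odds ratio of 2 the assumed patterns give 1.83 to 1.35. With a weak relation the bias is small (1.64 for a true 1.71), and with none it is zero. The document does not give the relation, so the actual size for any drug cannot be stated.

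A reader might infer that the Cox model is also pulled toward 1, or ought to be stratified by matched set. The documents do not support either. That approach matches on exposure, where a Cox model that ignores the matching validly estimates a marginal hazard ratio. Its unstated variance method is detail that an article may leave out, and stratifying by pair lowered power in two of the three simulated settings. Nor do the figures support a general loss of power: it is confined to drugs whose use follows a matching factor strongly, and it matters mainly where numbers are small.

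**What to change.** In the Statistical Analysis section and the Methods paragraph of the Abstract, separate the two approaches. For the comparison of survivors with non-survivors, state that the odds ratio always conditions on the matching factors, regardless of balance:

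- conditional logistic regression on the matched sets if matching is individual;
- logistic regression that includes all matching factors if matching is by frequency.

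Keep the conditional rule (suspected residual confounding or remaining imbalance) only for covariates beyond the matching factors. Apply the same analysis to the replication in both control groups, so that the decision to discard a finding rests on comparable estimates.

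The cost is a change of wording and standard R functions, with no new data. There is a small downside: pairs concordant for exposure do not contribute to the conditional estimate, and rarely used drugs may need exact or category-adjusted models.

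Nothing has to change for the Cox model. Covariate adjustment, or standard errors clustered on the matched set, is an optional gain in efficiency there.

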As a secondary objective, we plan to analyze the relationship between the presence of various nonneoplastic diseases and the survival of patients with cancer. To do this, we will compare the survival of patients with a specific disease to those who do not have it, adjusting multivariate models for age, gender, other conditions that may impact survival, and medications that have previously been shown to modify survival in previous analyses.

All analyses conducted in the cohort of patients with cancer will be replicated in a control patient group matched by age to the patients with cancer (with expected lower mortality) and in another group of older patients, where each control will be 10 years older than their cancer counterpart (with expected higher mortality). The findings that are reproduced in these groups of the control cohort will be discarded, as they are considered the result of uncontrolled biases or general effects on survival, not related to the cancers under study.

To consider a result statistically significant, the P value will be set at P=.05. All analyses are considered exploratory and hence subject to confirmation in new studies; therefore, no correction techniques will be applied to the P values obtained. All statistical analyses will be performed using R statistical software (version 4.1.0 or higher; R Core Team).

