### Methods to Address Potential Sources of Bias

This study, given its retrospective nature, is potentially affected by a series of biases, whose prevention or compensation will be attempted through various techniques. The 3 most important biases are discussed below:

Reverse causality bias: drugs that are prescribed to patients near death to control their symptoms will appear associated with an increased risk of death in the analyses, with the prescription of these drugs not being the cause of death but a consequence of proximity to death. This bias will be alleviated by eliminating the drugs prescribed 3 months before death from the analysis.“Immortal patient” bias: the longer a patient survives, the more likely he or she is to be diagnosed with pathologies and to consume drugs. This can give the false appearance that the drugs consumed throughout life are the cause of prolonged survival. To control this effect, the analyses only considered the drugs consumed up to a certain date in the group of patients who survived until that same date. For example, in the group of patients who have survived at least 3 months after the diagnosis of their cancer, only drugs consumed at any time up to month 3 after the cancer diagnosis will be considered. Thus, the consumption of the drug will not be explained by longer survival because the entire group will have survived until the moment when the drugs under study are consumed. Patients who consume the study drugs after the established time cutoff point will be eliminated from the analysis. As a comparison group, only patients who have not consumed the drug at any point in their disease evolution will be taken into account.Diagnostic anticipation or “medical surveillance” bias: this bias occurs when patients are included in studies who are in a screening program for cancer because, in such programs, the cancer is diagnosed earlier, which causes the erroneous impression that the individuals live longer. In our database, patients with certain diseases may have undergone frequent diagnostic tests, thus triggering early cancer detection. For example, patients with chronic obstructive pulmonary disease (COPD) may have undergone periodic radiographs, in which lung cancer has been detected early. This may give the impression that COPD, or the drugs used by patients with COPD, are associated with increased survival from lung cancer. To control this bias, patients with a previous pathology that produces greater medical surveillance of the organ where the cancer developed will be eliminated from the analysis.

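### Drug users are compared with never-users whether or not those have the drug's indication, and the indication is not a named matching variable, so a cancer-specific disease effect may be credited to the drug

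*Protocol article*

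**What the plan says.** All references are to the protocol article.

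- **Contrast.** Under Statistical Analysis, one approach compares "the survival time of participants exposed and unexposed to each drug available in the database", and likewise for each drug family. The other compares the exposure odds of 5-year survivors and of patients who died.
- **Comparator.** Methods to Address Potential Sources of Bias states: "As a comparison group, only patients who have not consumed the drug at any point in their disease evolution will be taken into account". Patients who start the drug after the time cutoff are removed. The drug's indication is not mentioned.
- **Matching and adjustment.** In both approaches "matching will be carried out between the groups with respect to confounding variables"; the variables are not listed. If residual confounding is suspected or imbalance remains, "adjustments for age, sex, and diagnostic groups will be performed". The article does not say whether diagnostic groups are tumour types or comorbidities.
- **Disease models.** The secondary objective relates nonneoplastic diseases to cancer survival, "adjusting multivariate models for age, gender, other conditions that may impact survival, and medications that have previously been shown to modify survival" in earlier analyses.
- **Control cohort.** All analyses are repeated in two cancer-free groups. "The findings that are reproduced in these groups of the control cohort will be discarded", being regarded as "uncontrolled biases or general effects on survival, not related to the cancers under study".
- **Listed biases.** Three are treated: reverse causality, immortal time and medical surveillance. Confounding by indication is not among them.

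**The concern.** For a drug with a specific indication, most users have the disease and many never-users do not. Unless the groups are balanced on that disease, the contrast mixes the effect of the drug with the effect of the disease.

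The protocol recognises this route in one direction only. Its disease models adjust for other conditions and for drugs, but no matching statement is made for the drug models, which serve the primary objective. On chronic obstructive pulmonary disease (COPD) it says: "This may give the impression that COPD, or the drugs used by patients with COPD, are associated with increased survival from lung cancer". That accepts that a disease can make its drugs look beneficial, but the remedy given addresses only earlier detection through surveillance.

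At stake is which drugs are put forward for trials. An inert drug could be nominated, or labelled harmful, because of the disease it treats. The error could also carry over: a drug flagged for this reason would enter the disease models as an adjustment variable and absorb part of that disease's own effect. This is a systematic error, so a larger database does not reduce it.

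**Working it through.** **1. The plan's own figure.** Sample Size Considerations gives 294 per group for 20% versus a 10-point difference, 5% significance and 80% power. With 30% as the alternative, two-sided, pooled variance and no continuity correction:

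n = [1.96·√(2·0.25·0.75) + 0.8416·√(0.2·0.8 + 0.3·0.7)]² / 0.10² = (1.2002 + 0.5119)² / 0.01 = 293.1, rounded up to 294. Power at 294 is 80.1%. The figure reproduces, and its scale is used below.

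**2. What each safeguard reaches.**

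| Safeguard | Reaches the indication? |
|---|---|
| Matching on confounding variables | Possibly; the set is not listed |
| Conditional adjustment for age, sex, diagnostic groups | Only if diagnostic groups means comorbidity |
| Replication in people without cancer | Only if the disease has a similar effect there |
| Surveillance exclusion | Only diseases that increase monitoring of the cancer organ |
| Removal of late starters | No; it addresses timing of use |

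What none of them is certain to remove is a disease effect specific to patients with cancer that does not act through surveillance. The Results section itself expects disease associations in different cancer types and effects specific to particular cancers.

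**3. Illustration for an inert drug, with no safeguard operating.** From the article: 20% survival, 294 per group, P=.05. Assumed, because the article gives no values: disease prevalence d; drug use u1 in those with the disease and u0 in those without; a shift Δ in 5-year survival due to the disease.

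- Share with the disease among users: a = d·u1 / [d·u1 + (1−d)·u0]
- Share among non-users: b = d·(1−u1) / [1 − d·u1 − (1−d)·u0]
- False survival difference: Δ·(a − b)

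Worked case with d = 0.20, u1 = 0.60, u0 = 0.02:

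- a = 0.12/0.136 = 0.882; b = 0.08/0.864 = 0.093.
- Δ = −0.10: survival is 0.112 in users and 0.191 in non-users, a difference of −0.079. The standard error is 0.02955 under the null and 0.02937 under the alternative, so the chance of P<.05 is Φ[(0.0790 − 1.96·0.02955)/0.02937] = Φ(0.72) = 76%.
- Δ = +0.10: 0.288 versus 0.209, significant in 60% of tests.

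Grid: d = 0.10, 0.20, 0.30; (u1, u0) = (0.6, 0.02), (0.4, 0.02), (0.6, 0.1), (0.3, 0.05); both signs of Δ.

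| Disease effect | False difference, points | Significant at 294 per group |
|---|---|---|
| 10 points | 3.2 to 7.9 | 16% to 76% |
| 5 points | 1.6 to 4.0 | about 8% to 24% |

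At an assumed 2,000 per group, the 5-point effect with the 88% versus 9% split makes the inert drug significant in about 85% to 91% of tests. The article reports 102,860 patients, so some contrasts may be that large or larger.

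**4. With the indication balanced.** If a = b, the false difference is Δ·0 = 0 and the inert drug returns to the nominal error rate, whatever Δ is.

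**The case against.** The strongest reply is that the plan already covers this. Matching is promised in both approaches; a disease that drives both prescribing and survival is by definition a confounding variable; and diagnosis lists are collected for everyone (Outcome Variables and Measurements). The Introduction calls this a general protocol and leaves methodological detail to separate papers, and one matching list could not fit every drug. General disease effects on mortality are the target of the cancer-free replication, and patients with COPD and lung cancer, the protocol's own example, would be excluded.

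Much of this stands. A reader might infer that users are simply compared with every non-user, so that the disease effect necessarily ends up in the drug estimate. The documents do not support that: matching could include the indication, late starters are removed, and two further filters apply. An unlisted matching set would, by itself, be detail that an article may omit.

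What does not fall away is what the article fixes. The comparator is defined by never having taken the drug, and the only adjustment variables named for drug models are age, sex and an undefined diagnostic grouping. Adjustment for other conditions is stated for the disease models alone. By its own description, the control-cohort filter is aimed at effects unrelated to the cancers under study.

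The illustration is also open to challenge. A 10-point disease effect equals the whole difference the study is sized to detect, and a 10-point loss is impossible for the cancers in Table 2 with survival of 5%, 5.2% or 8.2%. With the 88% versus 9% split at 294 per group, a 3-point effect gives about 11% and a 2-point effect about 8%. That is a fair limit on the size, not on the mechanism.

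Finally, labelling the analyses exploratory and requiring confirmation limits the consequences, but it does not answer a systematic error in choosing which drugs go forward.

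**Conclusion.** The point holds in a limited form. The plan neither restricts the comparator to patients with the drug's indication nor names the indication as a matching or adjustment variable. Where matching does not balance it, a disease effect specific to patients with cancer and not linked to surveillance may be credited to the drug.

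The ranges of 16% to 76% (10-point effect) and about 8% to 24% (5-point effect) should not be read as the plan's false-positive rate. They rest on assumed prevalence, drug use and disease effects, equal groups of 294, and no matching, adjustment, exclusion or control filter. They show that the error can be material and grows with group size. Nor do the documents show that the primary analysis would largely restate the secondary one.

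The change should be made. It is more than missing detail, because a better confirmatory contrast is available from data already collected.

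**What to change.** Keep the never-user contrast as the first screen. For each drug that passes it and has an identifiable indication, repeat the analysis among patients with that indication recorded by the landmark date, using the hospital and primary care diagnosis lists. Alternatively, make the indication and comorbidities mandatory matching variables for that drug. Nominate the drug only if the association persists. Add confounding by indication to the listed biases and define diagnostic groups.

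Report comparison with other agents of the same ATC4 family as supportive only. As a condition for nomination it would cancel a true class effect, which the family-level analyses are meant to find.

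Cost: protocol or SAP wording, a drug-to-indication map and further model runs on existing data. Downsides: fewer comparators and wider intervals. Untreated patients with the indication may differ in severity, so some confounding can remain. Drugs with no recorded indication, or with many, keep only a screen result and should be labelled as such.

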### Outcome Variables and Measurements

The primary end point is survival, calculated from the date of entry in the database until death or until 5 years of follow-up are reached. For patients in cohort 1, the earliest date of cancer diagnosis for which they have been selected to be part of the cohort will be considered the date of entry into the study (inclusion criterion).

As study variables, the following data will be collected from all patients:

List of diagnosed diseases (data source: CMBD and ICS ECAP diagnostic registry)Date of death (data source: INE cause of death registry)Cause of death (data source: INE cause of death registry)Pharmacological treatment (data source: Catalan electronic prescription), including all prescribed active ingredients, drug withdrawal dates from pharmacies, consumed doses, and prescribed regimen, during the entire follow-up periodSex (data source: Sistema Integral d'Informació de Salut)Date of birth (data source: Sistema Integral d'Informació de Salut)Basic health area (data source: Sistema Integral d'Informació de Salut)

For the patients included in the study with one of the cancers under study (cohort 1), the following variables will also be collected:

Type of cancer and presence of metastases (data source: CMBD and ICS ECAP diagnostic registry)Date of diagnosis for which the patient is included in the cohort (data source: CMBD and ICS ECAP diagnosis registry)Surgical treatment of the cancer (data source: CMBD)Date of surgical treatment (data source: CMBD)

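### The secondary analysis sets no diagnosis-date limit on the disease exposure, and the plan's immortal-time control is worded for drugs only

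*Protocol article*

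**What the plan says.** All references are to the protocol article.

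- **Exposure (Statistical Analysis).** For the secondary objective, "we will compare the survival of patients with a specific disease to those who do not have it". Adjustment is for age, gender, other conditions and "medications that have previously been shown to modify survival in previous analyses". No diagnosis window, landmark or time-dependent term is given.
- **Source (Outcome Variables and Measurements).** The variable is "List of diagnosed diseases (data source: CMBD and ICS ECAP diagnostic registry"), with no restriction to codes before entry.
- **Time zero (same section).** Survival is "calculated from the date of entry in the database until death or until 5 years of follow-up are reached". For the cancer cohort, entry is the earliest qualifying cancer diagnosis.
- **Bias (Methods to Address Potential Sources of Bias).** The immortal-time item says that "the longer a patient survives, the more likely he or she is to be diagnosed with pathologies and to consume drugs". The remedy is that "the analyses only considered the drugs consumed up to a certain date in the group of patients who survived until that same date". The worked example is again about drugs: "only drugs consumed at any time up to month 3 after the cancer diagnosis will be considered". Patients who start the drug after the cutoff are removed, and the comparators are those who never used it.
- **Filter (Statistical Analysis).** All cancer-cohort analyses are repeated in two control groups, and findings that recur there are dropped.

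**The concern.** The plan names two things that accumulate with survival, diagnoses and drugs, and then restricts only drugs. If disease status is read from the full record, a patient must live until the diagnosis date to enter the disease group, but is counted as diseased from day 0. The event-free time before the diagnosis is credited to the disease, and patients who die early fall into the comparison group by default. Adjusting for age, gender and other conditions does not remove this.

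At stake are the secondary results. A chronic disease with no effect on death could be reported as associated with longer cancer survival, through the mechanism that the plan itself describes. Repeating the study with the same definition would give the same answer, so exploratory status does not protect against it.

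**Working it through.** **Plan's own figure.** The plan gives no figure for the secondary analysis. Its one calculation (Sample Size Considerations: 20% survival, 10-point difference, 5% significance, 80% power) reproduces. n = [1.96·√(2·0.25·0.75) + 0.8416·√(0.2·0.8 + 0.3·0.7)]² / 0.1² = (1.2003 + 0.5119)² / 0.01 = 293.2, hence 294 per group. It is unaffected by this point, and its 10-point difference serves below only as a yardstick.

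**Inputs.** From the documents: 5-year survival of 20% (the stated maximum) and 5% (lowest rounded value, metastatic bladder, Table 2), and 5 years of follow-up. Assumed, because the documents give no values: new-diagnosis rate r, share p with the disease at entry, constant hazards, diagnosis independent of death, true HR = 1.

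**Hand check (20% survival, r = 0.03, p = 0).**

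- Death hazard λ = −ln(0.2)/5 = 0.3219 per year.
- Ever diagnosed = r/(r+λ)·[1 − e^(−5(r+λ))] = 0.08525 × 0.8279 = 0.0706.
- Diagnosed and alive at 5 years = 0.2 × (1 − e^(−0.15)) = 0.0279.
- Apparent 5-year survival with the disease = 0.0279/0.0706 = 39.5%.
- Apparent survival without it = 0.2·e^(−0.15)/(1 − 0.0706) = 0.1721/0.9294 = 18.5%.
- False gap: 21 points.

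**Same case with p = 0.10.** Ever diagnosed = 0.1 + 0.9 × 0.0706 = 0.1635. Diagnosed and alive = 0.02 + 0.9 × 0.0279 = 0.0451. Survival is 27.6% against 18.5%, a false gap of about 9 points.

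**Cox HR, ever against never diagnosed** (400,000 simulated patients per setting; each cell is 20% survival / 5% survival):

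| At entry | 1% per year | 3% per year | 5% per year |
|---|---|---|---|
| 0% | 0.50 / 0.49 | 0.48 / 0.48 | 0.47 / 0.47 |
| 10% | 0.86 / 0.90 | 0.72 / 0.76 | 0.65 / 0.69 |
| 20% | 0.92 / 0.94 | 0.81 / 0.84 | 0.74 / 0.78 |

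At 40% prevalence the HR is 0.96-0.97 at 1% per year, 0.92-0.94 at 2% and 0.83-0.86 at 5%. Extending r to 10% per year lowers the bottom of the range to about 0.54 (10-20% prevalence), 0.71 (40%) and 0.43 (0%).

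**After the fix.** With disease status fixed at entry, HR is 0.99-1.02. With status taken at month 3 among patients then alive, and nobody removed for a later diagnosis, it is 0.96-1.03.

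**Does a small bias matter?** Take the mildest cell, HR 0.94 with 21.3% ever diagnosed. The variance of log HR is about 1/(D × 0.213 × 0.787), with D deaths. The expected z reaches 1.96 when D = (1.96/0.0619)²/0.1676, about 6,000 deaths. The database holds 102,860 patients, and P = .05 is applied without correction.

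**In controls.** With assumed 5-year survival of 60-95%, the same artefact gives HRs of 0.46-0.51, 0.59-0.87 and 0.68-0.91 at 0%, 10% and 20% prevalence.

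**The case against.** **The discard rule.** This is the strongest counter-argument. The artefact is about as large in controls as in cancer patients, so many harmless diseases that look protective would be dropped. A reader might infer that the whole secondary objective is biased; the rule means the documents do not support that. What remains is that the rule filters findings without correcting estimates. It can miss a disease diagnosed more often during cancer follow-up than in controls, and it also drops genuine effects present in both cohorts.

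**Silence is not a rule.** The plan does not say that follow-up diagnoses count. The phrase about the entire follow-up period is attached to drug treatment, the primary-care record is described as including previous illnesses, and the Results section speaks of chronic diseases. The article also defers substudy details to later papers. Reading disease status as pre-existing is therefore plausible, and the bias is conditional. The point still stands, because this article names the diagnosis mechanism and then controls only the other exposure. The Discussion's remark on shortening the time frame refers back to those controls and gives no disease rule.

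**Size.** A reader might take an HR near 0.5 as typical. That needs nobody to have the disease at entry, which is implausible for chronic disease. Even then, if diagnosis rates rise tenfold in the last 3 months of life, the HR is 0.71-0.79. The direction does not change.

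**Medication adjustment.** A reader might also infer that adjusting for survival-modifying drugs is an error because they lie on the disease's causal path. The documents do not give the timing of those drugs or say why they were started. Whether to estimate a total or a drug-independent association is a choice of estimand.

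**Conclusion.** The concern holds in conditional form. The text leaves the disease exposure without a date limit and the stated immortal-time control does not reach it. If diagnoses after entry are counted, a harmless disease appears protective, with an HR of about 0.54-0.94 at 10-20% prevalence at entry and about 0.71-0.97 at 40%. The size is driven by the share of diagnoses made after entry: slight for mostly pre-existing disease, large for mostly new disease. The onset rates and prevalences are assumptions; only the survival values and follow-up length come from the article. The primary objective and the sample size are not affected. The plan should be changed on this point, but it does not invalidate the study.

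**What to change.** Add one sentence to the secondary-objective paragraph: a patient has the disease if a code for it is dated on or before the cancer entry date, and diagnoses first coded later enter only as time-dependent covariates. In the control cohort, apply the same rule at the control's entry date.

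A landmark is an acceptable alternative: classify disease status at the landmark among patients alive then, and keep those diagnosed later in the group they belonged to at the landmark. The drug rule should not be copied as it stands. It removes people exposed after the cutoff and uses never-exposed comparators, so group membership depends on what happens after the landmark.

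Optionally, show a model without post-entry medications beside the medication-adjusted one, stating which association each estimates.

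The cost is small, because Data Curation already attaches a date to each event. The downside is that diseases first recorded after entry are no longer analysed as fixed exposures. The Results section says analyses have begun, so the definition should be settled before secondary results are reported.
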